### Sample size

Sample size calculations have been carried out with PASS 13 Power Analysis and Sample Size Software [PASS 13, 2014] using the formula of Schoenfeld [26]. In a non-randomized clinical trial at the university hospital Essen with 402 melanoma patients, we observed a five-year distant metastasis-free survival cumulative survival probability of 67% determined using the Kaplan–Meier product limit estimator for patients after standard SLNE (n = 254, 46% with T2 and 31% with T3) which is in line with Morton et al. [27]. In the SNEPS trial, we intend to include patients of stages I and II but with an expected classification of mainly stage II or III after postoperative histology. We therefore assume to observe a comparable treatment effect in the control group. For patients with SPECT/CT-aided SLNE (*n* = 148), we observed a five-year distant metastasis-free survival cumulative survival probability of 77% in the non-randomized clinical trial. This corresponds to a HR of 1.56 (95% CI 1.06–2.30). This HR seems relatively large at first sight, but given the high distant metastasis-free survival rates it is equivalent to a difference in five-year distant metastasis-free survival of 10%, which is rather small for such a late time point, but still clinically relevant and in the range of generally accepted effect sizes in oncology trials.

The sample size calculation is based on the intention to compare the distant metastasis-free survival times in both groups with the partial likelihood method of Cox [21] that tests whether the regression coefficient from a Cox proportional hazards model [28] is equal to zero and that coincides with the log-rank test [24]. Given the two-sided version of this test with a significance level of 5% and assuming a true HR of 1.56, 214 events have to be observed in total to achieve a power of 90%, 126 in the control group, and 88 in the experimental group. These results assume that the HR is constant throughout the study. For the anticipated proportion of patients having a distant metastasis during the study, we assume 33% in the control group and 23% in the SPECT/CT-aided group. Thus, 380 evaluable patients per group (760 in total) have to be recruited. To account for 10% dropouts or loss of information because of non-compliance to follow-up visits, a total of 836 patients will be randomized.

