### Randomization

Patients with malignant melanoma are allocated by 1:1 randomization to be treated with SLNE with or without preoperative hybrid SPECT/CT.

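### The 10% dropout allowance is applied as 760 × 1.10, so 836 randomized patients cover a loss of about 9%, not 10%

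*Protocol article*

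**What the plan says.** All figures are in the Sample size section of the protocol article unless noted.

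- The calculation was done "using the formula of Schoenfeld", two-sided at 5%, "assuming a true HR of 1.56".
- The event requirement is given as "214 events have to be observed in total to achieve a power of 90%, 126 in the control group, and 88 in the experimental group".
- For the proportions of patients with a distant metastasis during the study, "we assume 33% in the control group and 23% in the SPECT/CT-aided group".
- From these the section concludes that "380 evaluable patients per group (760 in total) have to be recruited".
- The last step is the inflation: "To account for 10% dropouts or loss of information because of non-compliance to follow-up visits, a total of 836 patients will be randomized".
- Allocation is 1:1 (Randomization).
- All randomized patients belong to the intent-to-treat set (Methods against bias). The primary endpoint is treated as either an event or a censored time, so it is never missing (Statistical methods).

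The section does not say whether the 10% refers to the randomized or to the evaluable number.

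**The concern.** Dropouts come out of the randomized group. If a fraction *d* of those randomized is lost, the number remaining is N × (1 − *d*), so the required total is the evaluable number divided by (1 − *d*). Multiplying by (1 + *d*) gives a total that is slightly too small. The number 836 matches the multiplication exactly. On the ordinary reading, the three stated figures (760 evaluable, 10% loss, 836 randomized) therefore cannot all hold.

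What is at stake is the accuracy of a stated design figure. Someone tracking losses during the trial would count them against the randomized total and take 10% as covered, when the margin for 760 evaluable patients ends at 9.1%.

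**Working it through.** **Inputs (Sample size and Randomization sections).** Two-sided α = 0.05; power 90%; hazard ratio 1.56; event proportions 33% and 23%; 1:1 allocation; 760 evaluable; 10% loss; 836 randomized. The mean event proportion is (0.33 + 0.23) / 2 = 0.28.

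**1. Reproducing the plan's figures.**
- Schoenfeld events: 4 × (1.960 + 1.282)² / (ln 1.56)² = 212.5, rounded up to 213.
- Patients: 213 / 0.28 = 760.7, about 380 per group. This agrees with the stated 760.
- Expected events by arm: 380 × 0.33 = 125.4, rounded up to 126; 380 × 0.23 = 87.4, rounded up to 88. The sum is the stated 214. Without rounding, 760 patients give 760 × 0.28 = 212.8 events.
- Randomized total: 760 × 1.10 = 836. This reproduces the stated figure exactly.

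**2. The dropout step.**
- Needed for a 10% loss among those randomized: 760 / 0.90 = 844.4, so 845, or 846 for two arms of 423.
- Left after a 10% loss from 836: 836 × 0.90 = 752.4, about 752, which is 8 short of 760.
- Loss that 836 does cover: (836 − 760) / 836 = 76 / 836 = 9.1%.

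**3. Effect if dropouts contribute nothing.** Power is Φ(√D / 2 × ln 1.56 − 1.960), where D is the number of events.

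| Evaluable patients | Expected events (× 0.28) | Power |
|---|---|---|
| 760 | 212.8 | 90.03% |
| 752.4 | 210.7 | 89.75% |
| Difference | 2.1 | 0.28 points |

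**4. Effect if dropouts are followed for part of the time.** This is an illustration. Its assumptions are exponential event times matching 33% and 23% over five years, and the 10% loss spread evenly over those five years.
- With cumulative hazard H = −ln(1 − p), the average event probability before loss is 1 − p / H. Control: 1 − 0.33 / 0.4005 = 0.176. SPECT/CT: 1 − 0.23 / 0.2614 = 0.120. The mean is 0.148.
- Dropouts number 836 × 0.10 = 83.6 and contribute 83.6 × 0.148 = 12.4 events.
- Total: 210.7 + 12.4 = about 223 events, with power of about 91%.

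Under the same hazards, the gap to 212.8 events closes once dropouts have been followed for about 5 months on average, and the gap to 214 at about 7 months.

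**The case against.** **The base of the 10% is not stated.** If it means 10% added to the evaluable number, 836 is consistent. That is possible, but the sentence speaks of 10% dropouts, and a dropout rate is normally a share of those randomized. If the add-on was meant, the sentence should say so; the loss covered would still be 9.1% of those randomized.

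**The intent-to-treat analysis loses nobody.** This objection largely stands as regards the consequence. Patients lost during follow-up remain in the Cox model until censoring, and their earlier events count. Withdrawals between randomization and surgery, which the Statistical methods section anticipates, would add almost nothing. The allowance, however, also covers non-compliance with follow-up visits, and such patients are partly observed. The 752 is therefore a worst case. What remains is that the section plans in evaluable patients and inflates for loss of information, and within that premise the step is miscalculated.

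**It is about 1% of the sample.** Correct: 9 to 10 patients in 836, against a planning rate that is itself a round number.

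**A stronger reading.** A reader might infer that 836 patients cannot deliver the 214 events or the 90% power, and might count 3 to 4 missing events. The documents do not support this. That count sets an unrounded 210.7 against a 214 obtained by rounding up in each arm; the like-for-like comparison is with 212.8, and the unrounded Schoenfeld requirement is 212.5. It also assumes that every dropout contributes no information, which is not how the primary analysis treats them.

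**Conclusion.** The point holds as a minor correction of a stated figure. On the ordinary reading of a dropout rate, 836 randomized patients leave about 752 evaluable after a 10% loss, and the stated 760 is secured only up to a loss of 9.1%. The cost is at most about 2 expected events and 0.3 points of power, at the plan's own hazard ratio and event proportions and with dropouts contributing nothing. Even then power rounds to the stated 90%. In the planned analysis the cost is smaller, and with partial follow-up it may vanish. The finding does not show that the trial is underpowered, and it neither depends on nor adds weight to any question about the other sample size assumptions.

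**What to change.** Keep 836 and change the stated allowance in the Sample size section to about 9% of those randomized (76/836 = 9.1%). This is a one-line edit that adds no patients and leaves the 760 evaluable patients and 214 events as they stand.

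Two alternatives are less suitable. Restating the evaluable number as 752 with about 211 expected events would conflict with the 214 events that the same section requires. Raising the total to 846 would add 10 patients to a trial already recruiting (Trial status), for at most about 0.3 points of power.

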## Discussion

In this multi-center, unblinded superiority clinical trial SPECT/CT-aided SLNE versus standard SLNE in melanoma patients will be compared. The primary efficacy endpoint is distant metastasis-free survival. Secondary endpoints comprise overall survival, disease-free survival, rate of local relapses within the follow-up period (false-negative rate of SLN), number of positive SLN (sensitivity, false-positive rate), complication rate, quality of life, quality-adjusted life years, inpatient days, and overall costs during hospital stays.

Because melanoma, depending on tumor depth, metastasizes early into regional lymph nodes [4], SLNE is probably the most important diagnostic and potentially therapeutic procedure for melanoma patients. Recommendations for the use of SLNE for primary melanoma are therefore included in the current American Joint Committee of Cancer guidelines.

All study patients will at least receive the gold standard (lymphoscintigraphy). However, this procedure has resulted in some controversies in international discussions [29, 30]. Therefore, two diagnostic modalities will be compared. In the experimental study, one group of patients will additionally receive SPECT/CT. No additional risk is expected. From the experts of the German Association for Radiology, the radiologic diagnostic procedures in this study are evaluated as being according to medical standard so that no approval from the federal authority for radiation protection is required. Central ethical approval has been confirmed from Institutional Review Board of the University Hospital Essen (ref. approval no. 18–8288-BO) and we will not begin recruiting at other centers in the trial until local ethical approval has been obtained.

All investigators and the involved contract research organization (Alcedis GmbH, Gießen) ensure that the requirements of the World Medical Association Declaration of Helsinki are met and that the conduct of the trial is in accordance with current ICH guidelines for good clinical practice.

### Methods against bias

After initiation of the sites, all patients will be consecutively screened and all eligible patients willing to participate will be included in the trial. In order to achieve comparable groups regarding possibly relevant predictors and achieve balanced group sizes per site, patients will be allocated in a concealed manner by central web-based preoperative 1:1 stratified (minimization algorithm [Pocock and Simon] with biased coin principle) randomization with stratification factors site, sex, tumor depth (< 4.0 mm or ≥ 4.0 mm), and tumor location (head and neck region, yes or no). The primary analysis will control for the factors of the randomization. Each patient who is registered will be randomized and each randomized patient is part of the intent-to-treat analysis. It is not feasible to blind the patient or initial reader of the SPECT; however, physicians responsible for the follow-up and detection of distant met\astases will be blinded against the SPECT status by non-accessibility of the SPECT electronic case report form. In addition, the local interdisciplinary tumor board and an independent endpoint committee will review written reports of potential outcomes. The surgical technique will be identical in all participating sites and only operating physicians with a cumulative experience > 100 SLN surgical procedures will participate. The impact of a learning curve is thereby small. Performance bias will be avoided to a certain extent by certifying only experienced surgeons. All participating sites in Germany are certified by OncoZert and have a quality management system. All clinical investigators involved in this trial are experienced in performing SLN surgery, using preoperative SPECT/CT imaging and are trained in Good Clinical Practice. This allows for reduction of interrater variability to a minimum.

## Trial status

Protocol version 1.1 (19. September 2018). The trial began recruitment on 25 September 2018 and is currently ongoing.
